## Abstract

**Introduction::**

Recurrent ischemic strokes (IS) make up to one-third of all strokes. Nine out of 10 strokes are due to modifiable risk factors. Thus, it seems that standard management strategies of modifiable risk factors are yet to improve. Hence, we planned a randomized controlled trial assessing nurses or pharmacists-led aggressive control of comorbidities and their prognostic impact on IS and transient ischemic attacks (TIA).

**Methods/design::**

Prospective study to optimize the health of patients with TIAs and stroke admitted to the Hamad General Hospital (PROMOTE HEALTH) is an assessor-blinded, open-label, randomized, two-arm, controlled trial. Eligible patients have IS or TIA, and an additional modifiable risk factor (Hypertension or dyslipidemia) attending the stroke ward or clinic at the Weill Cornell-affiliated Hamad General Hospital. Stroke specialists will offer the control group the currently practiced best risk factor management strategies. Whereas, in the intervention arm, with the assistance of a nurse and a pharmacist, we will make aggressive attempts to meet targets of defined risk factors. The primary outcomes are the mean difference in blood pressure (BP) and low-density lipoprotein. Whereas myocardial infarction, recurrent stroke events, and mortality serve as the study's secondary outcomes. We require 200 patients per study arm to achieve a power of 80% and an alpha level of <0.05. The Medical Research Center and the Institutional Review Board have approved the study, and it was prospectively registered in a trial registry.

**Discussion::**

A significant proportion of strokes are due to modifiable preventable risk factors. Despite having the right preventive strategies aimed at mitigating these risk factors, a sizeable proportion of strokes are due to recurring events. This prompted the medical community to evaluate aggressive means of addressing these risk factors. The nurse or pharmacist-led management of comorbidities has been proven to be of value in the management of diabetes and hypertension. It will be of value to demonstrate the effectiveness of utilizing this additional task force in aggressively managing IS or TIA patients with an overarching goal of improving their prognosis. If our intervention proves to be efficacious, this would have a substantial impact on the current stroke practices and guidelines. Additionally, it will invite further research in the area.

**Clinical trial registration::**

Clinicaltrials.gov NCT02868723, last updated on September 2018

## Introduction

1

Cardiovascular disease accounts for more than 50% of deaths in the adult population, and its impact on society is immense.^[1]^ Cerebrovascular disease is a significant contributor to the problem, and its incidence is rising in the Gulf area population and around the globe. Evidence from multiple sources has shown that with aggressive risk factor management, stroke, especially recurrent stroke, is preventable.^[2]^ While there are recent studies from Qatar and the middle east on stroke subtypes, risk factors, hospital admission rates, and early prognosis, comprehensive research on the effects of prevention on disease progress or regression is urgently needed.^[3,4]^

We hypothesize that aggressive management of vascular risk factors to “recommended target levels” will lead to better vascular health. Compared to current practice, a comprehensive and coordinated approach at preventive measures will lead to more patients with better control of blood pressure (BP) and lipid levels. Improved risk factor management will result in slowing of atherosclerosis and its downstream effects, which will be measurable on sophisticated blood and imaging testing. Clinically this will translate into fewer hospital readmissions. Hence, we planned a randomized controlled trial to determine if a comprehensive and coordinated approach (led by nurses and pharmacists) at risk factor management will lead to more patients with better control of BP and lipid levels. Moreover, it will determine if better control of BP and lipid levels results in the slowing of plaque progression as measured on 3D Carotid Doppler imaging studies. Additionally, we will examine the effect of this approach on the mortality, stroke recurrence, and myocardial infarction incidence.

## Methods/design

2

### Study design and settings

2.1

This will be an open-label, two-arms, parallel, prospective randomized controlled study with a blinded assessment. We will recruit eligible patients admitted to the Weill Cornell affiliated Hamad General Hospital (HGH) or attending the Stroke Prevention Clinic with a diagnosis of ischemic stroke (IS) or transit ischemic attacks (TIAs). Potentially eligible patients will be invited to participate in our trial. If they agreed, they will be screened for eligibility and consented before being allocated to a study arm. The study is approved by the institutional review board (IRB) and the medical research center (MRC) of HGH. Additionally, it received an internal grant from the MRC (IRGC-2-NI-059). The trial is registered at clinicaltrials.gov (NCT02868723).

### Setting and participants

2.2

This is a single-center study. All patients with a first TIA or IS would be approached for participation in the study. Patients who, in addition, also have a history of hypertension or increased low-density lipoprotein (LDL) blood levels would be enrolled from the HGH inpatient wards and the Stroke Prevention/rapid access TIA Clinic. All patients will be screened for eligibility to participate in our study based on the following criteria:

**Inclusion criteria**

1.Ischemic stroke or TIA including ocular stroke such as Amaurosis Fugax, within the past year (not intracranial hemorrhage or due to trauma, malignancy or cardio-embolic related to structural heart disease)2.Meets at least one of the following three criteria:Systolic BP >140 mm Hg but <200 mm Hg average of 3 readings taken within 24 hours of admission and if based on clinic visits, then an average of three readings at least separated by 5 minutes-interval.Fasting LDL cholesterol >2.0 (measured within the previous 6 months)Total: HDL cholesterol ratio > 4.0 (measured within the previous 6 months)3.Willing to participate (by signing a consent form) and willing to return for study-related scheduled follow up visits for 1 year from the time of enrollment into the study.4.Age 18 to 90 years.

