**Exclusion criteria**

1.Participation in a concurrent interventional trial related to stroke or vascular disease.2.Any condition, including foreshortened life-expectancy, or severe comorbidities that would preclude treatment benefit or 12-month follow up.3.Institutionalized patients in a long-term care facility.4.Receiving maximal therapies for the inclusion comorbidity (3 maximal doses antihypertensives or maximal doses of statins.5.Computed tomography or magnetic resonance imaging shows evidence of primary intracranial hemorrhage or neoplasm.6.Active coronary artery disease.7.Severe renal disease on hemodialysis (HD) or severe hepatic dysfunction8.Decline of participation or inability to participate in our trial (Not able to follow in our center, or with cognition, mobility, or language barriers etc.).9.A severe systemic illness that will not allow for the patient to complete the 1-year trial.10.History of intolerance to statins or commonly used anti-hypertensive medications (intolerance/contraindication to statin (if elevated LDL-c is the inclusion criteria)11.Unable to tolerate antiplatelet agents.

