### Primary outcomes

2.6

The mean difference in the BP and LDL are the study's two primary outcomes.

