#### Analysis set

2.8.2

Intention to treat analysis will be utilized for all the study outcomes.

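### Entry needs only one uncontrolled risk factor, yet BP and LDL are each compared in everyone without stratifying or adjusting for entry status

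*Protocol article*

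**What the plan says.** **Entry.** Under Inclusion criteria, a patient with a qualifying stroke or TIA enters if he or she "Meets at least one of the following three criteria". The three are "Systolic BP >140 mm Hg but <200 mm Hg average of 3 readings", "Fasting LDL cholesterol >2.0 (measured within the previous 6 months" and "Total: HDL cholesterol ratio > 4.0 (measured within the previous 6 months".

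**Exclusions.** Item 4 of the Exclusion criteria removes patients "Receiving maximal therapies for the inclusion comorbidity". Item 10 concerns drug intolerance. It opens without a condition and then adds a parenthesis, "intolerance/contraindication to statin (if elevated LDL-c is the inclusion criteria", that ties the statin part to the LDL entry route.

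**Outcomes and analysis.** Section 2.6 makes "The mean difference in the BP and LDL" the two primary outcomes. Section 2.8.2 says: "Intention to treat analysis will be utilized for all the study outcomes". Section 2.8.3 names ANOVA or Mann-Whitney for continuous data and adds, without tying it to an outcome, that univariate and multivariate regression will be attempted. Section 2.3 describes variable-sized blocks and names no stratification factor. Section 2.8.1 bases 200 per arm on a 10% BP difference between the two groups, with 80% power, alpha 0.05 and 20% dropout.

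**The concern.** Eligibility is enriched for each risk factor separately, but the effect is measured across the pool. The intervention works by bringing uncontrolled risk factors towards target, so a patient already near target on one factor has less to gain on it. Taken literally, the criteria admit:

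- a patient with SBP 122 and LDL 2.6, who enters on LDL and counts in the BP comparison;
- a patient with SBP 165 and LDL 1.7, who enters on BP and counts in the LDL comparison;
- a patient with SBP 125, LDL 1.9 and ratio 4.3, who enters on the ratio alone and is below both thresholds that correspond to the primary outcomes.

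Item 4 shows that the authors had room to improve in mind, but it reaches only the entry factor. A patient who enters on BP may already take a maximal statin dose and is still scored on LDL. A patient who enters on LDL may already take three maximal antihypertensives and is still scored on BP.

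Two things are at stake. The average effect may be smaller than the effect in patients with the factor uncontrolled. Also, the spread between entry routes sits in the error term of an unadjusted test, although entry status is known before randomisation and costs nothing to use.

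**Working it through.** **1. The plan's own figure.** The dropout step is consistent: 160/(1 − 0.20) = 200 per arm. The 160 cannot be rebuilt, because no SD, baseline mean or control rate is given. With two-sided alpha 0.05 (sidedness is not stated) and 80% power, z = 1.960 + 0.842 = 2.80, and 160 evaluable per arm detect a standardised difference of d = 2.80 × √(2/160) = 0.313. If 10% means 10% of a mean SBP of 140–160, that is 14–16 mm Hg, and the implied SD is 14/0.313 to 16/0.313, about 45–51 mm Hg. With an assumed SD of 15–25, only 14–51 evaluable per arm would be needed. So the article does not show what effect, or what margin, the 200 represents.

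**2. Dilution.** Let f be the share of patients qualifying on the outcome in question, and r the effect in the others relative to qualifiers. Neither is given, so both are assumptions. With equal SD in both groups:

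- all randomised: z = 2.80 × [f + (1 − f)r];
- qualifiers only: z = 2.80 × √f;
- power = Φ(z − 1.96).

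This supposes that 200 per arm gives exactly 80% power when every patient carries the full effect.

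| f | All randomised, r = 0 | All randomised, r = 0.5 | Qualifiers only |
|---|---|---|---|
| 0.8 | 61% | 71% | 71% |
| 0.5 | 29% | 56% | 51% |
| 0.3 | 13% | 44% | 34% |

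For example, at f = 0.5 and r = 0, z = 2.80 × 0.5 = 1.40 and Φ(1.40 − 1.96) = 0.29.

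**3. When the restricted analysis is stronger.** Setting the two z values equal gives r = (√f − f)/(1 − f), which is 0.35 at f = 0.3, 0.41 at f = 0.5 and 0.47 at f = 0.8. Below that value the qualifier analysis has more power; above it the all-randomised analysis does. The article gives no basis for placing r on either side.

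**4. The same dilution under other readings of the 10%.**

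- If it is 15 mm Hg in qualifiers with an assumed SD of 20, then d = 0.75. At f = 0.5 and r = 0 the diluted d is 0.375, z = 0.375/√(2/160) = 3.35, and power is 92%. At f = 0.3 it is 52%.
- If it is already the difference expected in the mixed enrolled groups, the dilution is inside it and no further power is lost.

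**5. Avoidable variance.** If mean follow-up BP differs by Δ between patients who did and did not qualify on BP, an unadjusted comparison carries an extra variance of f(1 − f)Δ², which is 0.25Δ² at f = 0.5. Adjusting for the indicator removes this component. Adjusting for the baseline value can also remove predictable spread within each route. The same holds for LDL.

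**The case against.** The strongest reply is that an all-comer intention-to-treat comparison answers a legitimate question: what a coordinated strategy does for stroke and TIA patients with vascular risk factors. It is unbiased. Section 2.4 has the intervention address all of a patient's risk factors, not only the one that gave entry, and the article sets no numerical target. An entry threshold is therefore not the limit of possible benefit. All of this stands, and it is why the primary population should not be replaced.

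Four stronger readings are tempting, and the document does not support them.

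- **The trial is underpowered or will read as null.** This needs f, r and the meaning of the 10%, and none is given. Section 2.8.1 speaks of a difference between the study groups, which may already be the all-comer effect.
- **Each primary should be confined to qualifiers.** That changes the trial's question and has only 51% power at f = 0.5 and 34% at f = 0.3 under the calibration used above. It is the weaker analysis whenever r exceeds about 0.35–0.47.
- **Chance imbalance in entry route biases the result.** It adds variance, not bias.
- **Statin-intolerant patients may enter on BP.** Item 10 can be read either way. Section 2.2 also describes enrolled patients as having hypertension or raised LDL, which sits uneasily with entry on the ratio alone. The point does not depend on either case.

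It may also be said that stratification factors and covariates are details left to a fuller document, and that section 2.8.3 mentions multivariate regression. The first is fair, so nothing here rests on their absence alone. What the article does state is an unadjusted test as the comparison, and the regression is not attached to either primary outcome.

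**Conclusion.** The structure is as described: either/or entry, a maximal-therapy exclusion limited to the entry comorbidity, and both primaries compared in everyone by an unadjusted test. The consequence is loss of efficiency and a harder interpretation, not bias.

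Its size cannot be computed from the article. At f = 0.5 and r = 0, power is 29% if 200 per arm was sized for exactly 80% with every patient responding, and 92% if the 10% is 15 mm Hg in qualifiers with an assumed SD of 20. There is no further loss if the 10% is already the all-comer difference. All these figures assume two-sided alpha 0.05, 160 evaluable per arm and equal SDs. LDL above 2.0 may be met by more patients than SBP above 140, so BP may be the more diluted outcome; that is an inference.

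This is a worthwhile, nearly free improvement, not a defect that invalidates the design.

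**What to change.** 1. **Sections 2.6 and 2.8.2:** keep the all-randomised intention-to-treat comparison as primary for both BP and LDL.
2. **Section 2.3:** stratify randomisation by SBP above 140 (yes/no) and LDL above 2.0 (yes/no). Patients who enter on the ratio alone fall in the no/no stratum. If recruitment is complete, adjust each primary comparison in section 2.8.3 for these two indicators, preferably using the baseline value of the outcome.
3. **Section 2.8.3:** prespecify as supportive the comparison of BP in patients with SBP above 140 at entry and of LDL in patients with LDL above 2.0 at entry, each by allocated arm. Both sets are fixed before randomisation, so the randomised comparison is preserved.
4. **Section 2.8.1:** state that the 10% BP difference refers to the mixed enrolled population.

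**Cost:** a few sentences of protocol or SAP text, slightly more analysis work, and indicators already recorded at screening. The supportive subsets are smaller than the full sample and so less precise, and should be reported as such.

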### Interventions

2.4

After consent and initial evaluation and investigations, patients in the standard of care arm will have their risk factors managed according to the current protocols in place at the hospital in the prevention of recurrent stroke (Fig. 1). Whereas patients in the aggressive, coordinated management (intervention) arm will be offered a comprehensive review on mechanisms of stroke/vascular disease. Every attempt will be made to bring their risk factors to optimal control based on internationally accepted guidelines with assistance from a specially trained pharmacist and nurse practitioner. Both arms will be followed (initially every month for three months and then every three months) for one year. All stroke specialists will run the standard arm guided by HGH local protocol. Imaging studies and other tests completed at the start of the study will be repeated at the exit from the study one year following randomization. Smoking cessation programs will be offered to patients who continue to smoke, and regular exercise would be strongly encouraged. The Framingham Risk Score report cards would be discussed on each visit, which will include the status of risk factor management.

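### Clinic patients can enter on a lipid value up to 6 months old that predates their treatment, which dilutes the LDL primary outcome

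*Protocol article*

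**What the plan says.** The protocol article recruits from the inpatient wards and from the stroke prevention and rapid-access TIA clinic (sections 2.1 and 2.2). The index event may be old: "Ischemic stroke or TIA including ocular stroke such as Amaurosis Fugax, within the past year". Beyond that, the patient "Meets at least one of the following three criteria". The two lipid routes are "Fasting LDL cholesterol >2.0 (measured within the previous 6 months" and "Total: HDL cholesterol ratio > 4.0 (measured within the previous 6 months". The blood pressure route uses an "average of 3 readings taken within 24 hours of admission" for admitted patients and, "if based on clinic visits, then an average of three readings at least separated by 5 minutes-interval".

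Three other places bear on the point:

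- Exclusion criterion 4 removes patients already on maximal therapy for the qualifying condition. It does not remove patients whose lipids are controlled on less.
- Section 2.3 limits the time from screening and consent to randomisation to 48 hours. It sets no limit on the age of the qualifying measurement.
- Section 2.4 has tests at study start: "Imaging studies and other tests completed at the start of the study will be repeated at the exit from the study". Entry does not depend on their result.

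The primary outcomes are the mean differences in BP and LDL (section 2.6), analysed by intention to treat (section 2.8.2).

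**The concern.** The trial asks whether coordinated care brings BP and LDL under better control than usual care. For LDL, the patients who inform that question most are those whose LDL is above the cut-off when they are randomised. The entry rule does not select for that. It selects for a lipid value above the cut-off at some time in the past 6 months.

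In a ward patient just admitted, the two are nearly the same. In a clinic patient they can differ, because treatment started after the event may already have lowered LDL. Such a patient has less room to improve further in either arm, so the average LDL difference between arms shrinks. Intention to treat rightly keeps these patients in the analysis, so the loss has to be prevented at entry.

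**Working it through.** **Step 1. The plan's own figure.** Section 2.8.1 gives 200 per arm, 80% power, alpha 0.05, 20% dropout and a 10% BP difference. Evaluable per arm: 200 × (1 − 0.20) = 160. The article gives no standard deviation or control rate, so 200 can be neither confirmed nor refuted. No LDL effect is given either, so LDL power is unknown.

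**Step 2. Can a controlled patient pass every stated rule?** Take a clinic patient 5 months after a stroke.

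| Rule | Example | Outcome |
|---|---|---|
| Event within 1 year | 5 months ago | passes |
| LDL above 2.0, at most 6 months old | admission sample, 5 months old, above 2.0, before treatment | passes |
| Not on maximal statin dose | on less than that since the event | passes |
| Randomised within 48 hours of consent | yes | passes |
| LDL at randomisation | now at or below 2.0 | no rule |

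The ratio criterion has the same window and behaves the same way. The route has a limit: a value drawn before treatment for the event can count only if the event itself was within about the last 6 months. For older events, the qualifying sample must come after the event, though it may still precede a later change of treatment.

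**Step 3. Size of the dilution.** Let f be the share of randomised patients who entered this way with controlled lipids. As the extreme case, let them gain nothing, so the average standardised effect δ becomes (1 − f)δ. With n = 160 per arm and a two-sided 0.05 test,

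power ≈ Φ[(1 − f)δ / √(2/n) − 1.960].

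The effect that gives exactly 80% power is δ = √(2/160) × (1.960 + 0.842) = 0.313. Keeping 80% power multiplies the sample size by 1/(1 − f)².

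| f (assumed) | Φ argument | Power | Multiplier | Enrolled per arm to restore 80% |
|---|---|---|---|---|
| 0.1 | 2.521 − 1.960 = 0.561 | 71.3% | 1.235 | 200 × 1.235 ≈ 247 |
| 0.2 | 2.241 − 1.960 = 0.281 | 61.1% | 1.5625 | 200 × 1.5625 ≈ 313 |
| 0.3 | 1.961 − 1.960 = 0.001 | 50.0% | 2.041 | 200 × 2.041 ≈ 409 |

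**Step 4. How far this depends on assumptions.**

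- *Partial benefit.* If controlled patients gain a fraction g of the full effect, the factor is 1 − f(1 − g). With f = 0.2 and g = 0.5 it is 0.9, so power is 71.3% rather than 61.1%.
- *Larger effect.* A 10% difference on an assumed BP of 140 mm Hg with an assumed SD of 20 mm Hg gives δ = 14/20 = 0.7. On that scale δ/√(2/160) = 6.261. At f = 0.2 the argument is 5.009 − 1.960 = 3.049, power 99.9%. At f = 0.3 it is 4.383 − 1.960 = 2.423, power 99.2%.

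The loss is therefore large if the trial is only just powered for LDL, and negligible if the effect is large. The article does not show which applies.

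**The case against.** The strongest reply is that material harm is not shown. The share f is unknown, and Step 4 shows that a large effect would absorb it. Broad entry may also be deliberate, since section 2.2 describes patients with a history of hypertension or raised LDL. That limits the size of the point. The rule itself remains, and the article gives no reason for accepting old values from clinic patients.

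A second reply is that study-start values may already be the planned baseline, with the full protocol or SAP saying so. That is possible; the article does not name the baseline value. The part of the fix that concerns analysis may therefore only confirm existing intent. The entry rule, in contrast, is stated outright.

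A third is that the fix is partial. One criterion suffices while BP and LDL are both primary, so a patient who qualifies on BP may never have had raised LDL, and the reverse. This stands; fresh lipid samples do not remove that dilution.

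Stronger readings are tempting, but the documents do not support them:

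- *A reader might infer that falls from high qualifying values will pass for a treatment response.* For ward BP with no acute rise (assumed: admission mean 145, SD 20; later mean 145, SD 18; correlation ρ), selection above 140 and below 200 gives a later fall of about 12.7 − 11.4ρ mm Hg, or 8.1 to 4.7 for ρ from 0.4 to 0.7. That fall is expected equally in both arms and cancels in the randomised comparison. No within-arm response analysis is stated.
- *A reader might infer that controlled patients cannot benefit.* The outcomes are continuous means over a year of follow-up, so further lowering or better-maintained control can still separate the arms.
- *A reader might infer that ward BP must be confirmed after the first 24 hours.* That is a debatable recruitment trade-off; using one threshold in two settings is not a contradiction.
- *A reader might infer that setting is left unbalanced.* Randomisation balances it in expectation. The standard error of the difference in ward share is at most √(2 × 0.25/200) = 5 percentage points; with an assumed 15 mm Hg gap between settings, that is 0.05 × 15 = 0.75 mm Hg.

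**Conclusion.** The point holds for the lipid criteria in patients recruited from clinic. The stated windows admit patients whose lipids are already controlled, and no other stated rule stops them. The consequence is a smaller average LDL difference and less power, with no bias between arms. The illustrated fall in power to between 71% and 50% rests on three assumptions: affected shares of 10% to 30%, no gain at all in those patients, and exactly 80% power beforehand. With a standardised effect of 0.7 the same shares leave power above 99%. The change is worth making because it is cheap, not because a large loss has been demonstrated.

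**What to change.** **Eligibility.** For patients recruited from clinic, require the lipid criterion already stated (LDL above 2.0 or ratio above 4.0) to be met on the study-start sample, or on a sample taken after the index event on current treatment. Ward patients may keep the value from the current admission. A blanket refusal of values that predate treatment would bar valid admission samples in newly admitted patients.

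**Analysis.** In both settings, define baseline as study-start BP and LDL, not the qualifying values. Adjust the two primary comparisons for them and for recruitment setting (ward or clinic). Stratifying the randomisation by setting is optional.

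**If enrolment is complete,** make the analysis change alone. It improves precision but does not undo the dilution.

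**Cost.** Some extra screen failures among clinic patients. Where the study-start sample is used, its result must be available before randomisation, which section 2.3 places within 48 hours of screening and consent. LDL is not named among the study-start tests; since it is a primary outcome, I assume it is measured then, so no further blood test should be needed.
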